**1.3 TRIAL DESIGN**

This is a multicentre, randomised controlled, open label, investigator sponsored, two arms study.

Patients who satisfy all inclusion criteria and no exclusion criteria and have signed written informed consent, will be randomly assigned to one of the two treatment groups in a 1:1 ratio.

**2.0** **METHODS: PARTICIPANTS, INTERVENTIONS AND OUTCOMES**

**2.1 STUDY SETTING**

The study will involve 7 Italian Academic and non-Academic Internal Medicine Units, 2 Infectious Disease Units, 1 Respiratory Disease Unit.

See list of centres in APPENDIX 1.

**2.2 ELIGIBILITY CRITERIA**

**2.2.1 Inclusion Criteria (all required)**

1. Age > 18 and < 80 years
2. Positive SARS-CoV-2 diagnostic (on pharyngeal swab of deep airways material)
3. Severe pneumonia defined by the presence of at least one of the following criteria:
   1. Respiratory Rate ≥25 breaths /min
   2. Arterial oxygen saturation≤93% at rest on ambient air
   3. PaO2/FiO2 ≤300 mmHg
4. Coagulopathy, defined by the presence of at least one of the following criteria:
   1. D-dimer >4 times the upper level of normal reference range
   2. Sepsis-Induced Coagulopathy (SIC) score >4
5. No need for invasive mechanical ventilation
   - 1. **Exclusion Criteria**
6. Age <18 and >80 years
7. Invasive mechanical ventilation

3. Thrombocytopenia (platelet count < 80.000 mm^3^)

4. Coagulopathy: INR >1.5, aPTT ratio > 1.4

5. Impaired renal function (eGFR calculated by CKD-EPI Creatinine equation < 30 ml/min)

6. Known hypersensitivity to enoxaparin

7. History of heparin induced thrombocytopenia

8. Presence of an active bleeding or a pathology susceptible of bleeding in presence of anticoagulation (e.g. recent haemorrhagic stroke, peptic ulcer, malignant cancer at high risk of haemorrhage, recent neurosurgery or ophthalmic surgery, vascular aneurysms, arteriovenous malformations)

9. Concomitant anticoagulant treatment for other indications (e.g. atrial fibrillation, venous thromboembolism, prosthetic heart valves).

10. Concomitant double antiplatelet therapy

11. Administration of therapeutic doses of LMWH, fondaparinux, or unfractionated heparin (UFH) for more than 72 hours before randomization; prophylactic doses are allowed

12. Pregnancy or breastfeeding or positive pregnancy test

13. Presence of other severe diseases impairing life expectancy (e.g. patients are not expected to survive 28 days given their pre-existing medical condition)

14. Lack or withdrawal of informed consent

**2.3 INTERVENTIONS**

Patients who satisfy all inclusion criteria and do not have any exclusion criteria and have signed written informed consent, will be randomly assigned to a Low-Dose LMWH group (Control Group) or High-Dose LMWH group (Intervention Group).

The study is conceived as open-label: patients and all health-care personnel involved in the study will be aware of the assigned group. The treatments will be initiated as soon as possible after randomization (maximum allowed starting time 12h after randomization).

**Control Group** (Low-Dose LMWH): patients in this group will be administered Enoxaparin (Inhixa®) at standard prophylactic dose (i.e., 4000 UI subcutaneously once day).

**Intervention Group** (High-Dose LMWH): patients in this group will be administered Enoxaparin (Inhixa®) at dose of 70 IU/kg every 12 hours, as reported in the following table.

| **Body Weight (kg)** | **Enoxaparin dose every 12 hours (IU)** |
| --- | --- |
| <50 | 2000 |
| 50-69 | 4000 |
| 70-89 | 6000 |
| 90-110 | 8000 |
| >110 | 10000 |

The treatment with Enoxaparin will be initiated as soon as possible after randomization (maximum allowed starting time 12h after randomization). The treatment will be administered every 12 hours in the intervention group and every 24 hours in the control group.

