| **Statistical Considerations**  **& Sample Size** | **Statistical Considerations**  The efficacy will be assessed by estimating the difference between the two treatment arms in the proportion of participants experiencing clinical worsening during their hospital stay.  Safety will be assessed by estimating the difference between the two treatment arms in the proportion of participants who experience at least one bleeding event (major or non-major) during their hospital stay.  Relative risk (RR) will be used as measure of association, which will be reported with its 95% confidence interval.  The differences between the two arms in the variation of:   1. D-dimer level 2. Plasma fibrinogen levels   3) Mean platelet Volume  4) Lymphocyte/Neutrophil ratio  5) IL-6 plasma levels  at 3 time points (at randomization, at 48 hours and 96 hours) will be assessed.  These outcomes will be compared by using their mean values and summary indicators.  Overall survival, survival free from any cardiovascular event, such as Acute Myocardial Infarction [AMI], Objectively confirmed, symptomatic arterial or venous thromboembolism [TE] and survival free from need for either non-invasive or invasive mechanical ventilation will be also estimated. They will be reported by using Kaplan-Maier curves and compared by using hazard ratio (HR).  **Sample size**  300 participants will be needed to detect a relative reduction of 50% of clinical worsening. We hypothesized that the percentage of participants who experience clinical worsening in the LMWH low dose group would be around 25-30% and set an alpha error of 0.05 and beta-error of 0.20. | |
| **Treatment Schedule** | **Control group (Low Dose):** Enoxaparin (Inhixa®) 4000 IU subcutaneously once daily.  **Intervention group (High dose**): Enoxaparin (Inhixa®) 70 IU/kg subcutaneously twice daily.  Participants will receive the dose of Enoxaparin according to the protocol until the occurrence of at least one of the following events:   1. One of the events included in the primary outcome 2. Hospital discharge 3. Any adverse events and clinical condition requiring interruption of the scheduled intervention according to the judgement of the physician in charge | |

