**1.2 STUDY OBJECTIVE**

To assess whether high doses of Low Molecular Weight Heparin (LMWH) (i.e. Enoxaparin 70 IU/kg twice daily) compared to standard prophylactic dose (i.e., Enoxaparin 4000 IU once day) are:

1. more effective to prevent clinical worsening, defined as the occurrence of at least one of the following events, whichever comes first:
2. Death
3. Acute Myocardial Infarction [AMI]
4. Objectively confirmed, symptomatic arterial or venous thromboembolism [TE]
5. Need for either non-invasive - Continuous Positive Airway Pressure (Cpap) or Non-Invasive Ventilation (NIV) - or invasive mechanical ventilation for patients, who are in standard oxygen therapy by delivery interfaces at randomisation
6. Need for invasive mechanical ventilation for patients, who are in non-invasive mechanical ventilation at randomisation
7. Similar in terms of major bleeding risk

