**2.6 SAMPLE SIZE**

The target sample size is based on the hypothesis that LMWH administered at high doses versus low doses will significantly reduce the risk of clinical worsening. The overall sample size in this study is expected to be 300 with a 1:1 randomisation ratio. Assuming an alpha of 5% (two tailed) and a percentage of patients who experience clinical worsening in the control group being between 25% and 30%, the study will have 80% power to detect at least 50% relative reduction in the risk of death between low and high doses of heparin.

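### Below 50 kg the dosing table gives the high-dose arm the same daily enoxaparin dose as control (4000 IU), and no minimum weight keeps these patients out

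*Protocol*

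**What the plan says.** Section 2.3 (Interventions) gives the control dose as "4000 UI subcutaneously once day" and the intervention dose as enoxaparin "at dose of 70 IU/kg every 12 hours, as reported in the following table". The table has five weight bands, with these doses per injection: under 50 kg, 2000 IU; 50–69 kg, 4000 IU; 70–89 kg, 6000 IU; 90–110 kg, 8000 IU; over 110 kg, 10000 IU. On frequency the section states: "The treatment will be administered every 12 hours in the intervention group and every 24 hours in the control group".

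The Treatment Schedule in the synopsis has "70 IU/kg subcutaneously twice daily" and section 1.2 (Study Objective) has "Enoxaparin 70 IU/kg twice daily". Neither mentions bands or a lower weight limit. The eligibility criteria in the synopsis and in section 2.2 contain no minimum body weight, and the table itself provides a row for patients under 50 kg. Nowhere does the protocol describe that row as a deliberate dose reduction.

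**The concern.** The trial exists to compare a high with a standard prophylactic dose. For patients under 50 kg, twice the table entry equals the control daily dose. These patients would be randomised, labelled high-dose and analysed as such, while differing from control only in how the same 4000 IU is split over the day. They add patients to the efficacy and bleeding comparisons but no contrast in daily dose. The statement that the table reports 70 IU/kg is also wrong for this row, so a reader of the synopsis or objective would be misinformed about what the lightest patients receive.

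**Working it through.** **Inputs.** Table doses, control dose and frequencies: section 2.3. Sample size: section 2.6, "The overall sample size in this study is expected to be 300 with a 1:1 randomisation ratio", with two-sided alpha 5%, control rate 25–30%, 80% power and a 50% relative reduction. Assumptions of this review: 40 kg as a practical lower weight, the share of patients under 50 kg, and no treatment effect in that share.

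**Step 1: dose by band.** Dose per kg = row dose / weight. Daily dose = 2 × row dose, against 4000 IU a day in control.

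| Weight (kg) | IU per injection | IU/kg, low to high weight | IU per day | Ratio to control |
| --- | --- | --- | --- | --- |
| <50 (40 to 49.9) | 2000 | 50.0 to 40.1 | 4000 | 1 |
| 50–69 | 4000 | 80.0 to 58.0 | 8000 | 2 |
| 70–89 | 6000 | 85.7 to 67.4 | 12000 | 3 |
| 90–110 | 8000 | 88.9 to 72.7 | 16000 | 4 |
| >110 | 10000 | 90.9 downward | 20000 | 5 |

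The first row is the only one with a ratio of 1. It is 1 − 50.0/70 = 29% to 1 − 40.1/70 = 43% below the stated dose. A 2000 IU injection equals 70 IU/kg only at 2000/70 = 28.6 kg, an implausible adult weight.

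**Step 2: what 70 IU/kg would give.** At 40 kg: 70 × 40 = 2800 IU per injection, 5600 IU a day, 1.4 times control. Just under 50 kg: about 3500 IU per injection, 7000 IU a day, 1.75 times control. The table removes all of that increment.

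**Step 3: the plan's own sample size.** For 25% against 12.5% (two-sided 5%, 80% power, pooled-variance test of two proportions) 152 per arm are needed, 304 in total. This reproduces the stated 300 to within 2%. With 150 per arm,

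power = Φ{[√n·|p1 − p2| − 1.96·√(2p̄(1 − p̄))] / √(p1(1 − p1) + p2(1 − p2))}

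= Φ{[12.247 × 0.125 − 1.96 × 0.552] / 0.545} = Φ(0.824) = 79.5%.

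**Step 4: dilution.** If a share s weighs under 50 kg and gains nothing, the treated risk is p × [1 − 0.5 × (1 − s)]. For p = 0.25 and s = 0.01 this is 0.25 × 0.505 = 0.1263.

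| Assumed share under 50 kg | Power, control rate 25% | Power, control rate 30% |
| --- | --- | --- |
| 0% | 79.5% | 87.9% |
| 1% | 78.6% | 87.2% |
| 2% | 77.7% | 86.4% |
| 5% | 74.7% | 84.0% |

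**The case against.** The best reply is that the consequence is small. Power barely moves at 1–2%, and on the efficacy endpoint the dilution is towards no difference, not towards a false benefit. Even exact dosing at 70 IU/kg would give only 1.4 to 1.75 times the control daily dose here, against 2 to 5 times in the other bands. The schedules still differ. Body weight is recorded at screening (Appendix 2), so these patients can be identified and left out in a sensitivity analysis. All of this stands. It limits the size of the problem, but it does not create a daily-dose contrast where the table gives none.

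A reader might infer three stronger points, which the protocol does not support.

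- *That the 90–110 kg row is also an error, because it lies above 70 IU/kg throughout.* Its deviation of +4% to +27% is ordinary banding. Other rows deviate as much: +22% at 70 kg, −17% at 69 kg and about +30% just above 110 kg. The daily dose is four times control, so the contrast is intact.
- *That sites cannot tell whether the table or the per-kg figure applies.* Section 2.3 points to the table for the dose, and its column states the dose per 12 hours. The table reads as the operative instruction, and 70 IU/kg elsewhere as its nominal label.
- *That the randomised comparison is invalid or the sample size wrong.* Allocation is unaffected, and 300 reproduces from the stated inputs.

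**Conclusion.** The point holds for the under-50 kg row alone. As written, the statement that the table reports 70 IU/kg is wrong for that row, and an eligible subgroup is randomised with equal daily doses in both arms. The equality at 4000 IU a day follows from the protocol's own figures and needs no assumption. The 29–43% shortfall rests on the assumed 40 kg lower limit. The loss of power (79.5% to 78.6% or 77.7% at a 25% control rate) rests on an assumed 1% or 2% share and no effect in it. The protocol gives no weight distribution, so the actual loss cannot be fixed. This should be corrected because the intervention is misdefined for these patients; the power loss is a secondary matter.

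**What to change.** Add a minimum body weight of 50 kg to the eligibility criteria in the synopsis and in section 2.2, and delete the under-50 kg row from the table in section 2.3. Every remaining row is then at least twice the control daily dose. The cost is a short amendment, a notice to sites and the exclusion of light patients who would otherwise qualify, probably few.

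If the clinical team prefers to keep these patients, it should set the row near 70 IU/kg: about 2800–3500 IU per injection at 40–50 kg, or 5600–7000 IU a day. Moving up to the next table entry is not a good substitute: 4000 IU per injection would be 100 to 80 IU/kg at 40 to 50 kg, 43% to 14% above the nominal dose, in the lightest patients of a trial whose primary safety endpoint is major bleeding.

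Describing the regimen in the synopsis and objective as weight-banded, nominally 70 IU/kg, is optional wording. The 90–110 kg row needs no change.

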**Duration of treatments**

Patients allocated to the two arms will maintain the doses of Enoxaparin, as stated in the protocol, until:

1. hospital discharge

or

1. when at least one of the following events occurs:
2. Acute Myocardial Infarction [AMI]
3. Objectively confirmed, symptomatic arterial or venous thromboembolism [TE]
4. Need for either non-invasive - Continuous Positive Airway Pressure (Cpap) or Non-Invasive Ventilation (NIV) - or invasive mechanical ventilation for patients, who are in standard oxygen therapy by delivery interfaces at randomisation
5. Need for invasive mechanical ventilation for patients, who are in non-invasive mechanical ventilation at randomisation
6. Major bleeding
7. Any adverse events and clinical condition requiring interruption of the scheduled intervention according to the judgement of the physician in charge
8. Death

The decision about what type and dose of antithrombotic treatment to administer, after the interruption of assigned dose of Enoxaparin, will be left to clinical judgement of the physicians in charge.

Any information about the type and dose of antithrombotic treatments administered after the interruption of the assigned dose of Enoxaparin will be collected until the hospital discharge or death.

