| **Primary Study Objective(s)** | To assess whether high doses of Low Molecular Weight Heparin (LMWH) (ie. Enoxaparin 70 IU/kg twice daily) compared to standard prophylactic dose (ie, Enoxaparin 4000 IU once day) are:  a) more effective to prevent clinical worsening, defined as the occurrence of at least one of the following events, whichever comes first, during hospital stay:   1. Death 2. Acute Myocardial Infarction [AMI] 3. Objectively confirmed, symptomatic arterial or venous thromboembolism [TE] 4. Need for either non-invasive - Continuous Positive Airway Pressure (Cpap) or Non-Invasive Ventilation (NIV) - or invasive mechanical ventilation for patients who are in standard oxygen therapy by delivery interfaces at randomisation 5. Need for invasive mechanical ventilation for patients who are in non-invasive mechanical ventilation at randomisation 6. Similar in terms of major bleeding risk during hospital stay |  |
| **Secondary Study**  **Objectives** | To assess whether high doses of Low Molecular Weight Heparin (LMWH) (ie. Enoxaparin 70 IU/kg twice daily) compared to standard prophylactic dose (ie, Enoxaparin 4000 IU once day) differ in terms of the following events occurring during hospital stay:   1. Laboratory parameters of disease severity, including: 2. D-dimer level 3. Plasma fibrinogen levels 4. Mean Platelet Volume 5. Lymphocyte/Neutrophil ratio 6. IL-6 plasma levels 7. Clinically relevant non-major bleeding 8. Death during hospital stay and at 30 days 9. Acute Myocardial Infarction [AMI] 10. Objectively confirmed, symptomatic arterial or venous thromboembolism [TE] 11. Need for either non-invasive - Continuous Positive Airway Pressure (Cpap) or Non-Invasive Ventilation (NIV) - or invasive mechanical ventilation for patients, who are in standard oxygen therapy by delivery interfaces at randomisation 12. Need for invasive mechanical ventilation for patients, who are in non-invasive mechanical ventilation at randomisation | |

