**Criteria for discontinuing or modifying allocated interventions**

LMWH administration will start at the moment of randomization and will last until the hospital discharge, or up to the occurrence of any event included in the primary outcome.

Participants who during their hospital stay develop any new clinical condition, which require anticoagulant or antiplatelet treatment, such as atrial fibrillation and/or substitution of heart valves, will discontinue the allocated intervention and will be excluded from the study.

Discontinuation or modification of allocated interventions can also be warranted by the occurrence of one of the following events: any AE, including clinically relevant, non-major bleeding or clinically significant laboratory abnormality that, in the opinion of the Investigator, warrants the subject’s discontinuation, temporary or permanent, of study protocol-directed care.

Reasons for discontinuation or modification of allocated interventions and their dates will be collected and reported in the eCRF.

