**4.2 Statistical Methods**

All patients enrolled in the study will be entered in the full analysis set independently of his/her treatment time. The intention to treat population will be considered for primary analysis. A descriptive statistical analysis will be carried out to summarise every relevant variable. At baseline, categorical data will be summarised by using counts and percentages, whilst continuous variables will be presented using the number of patients, mean, standard deviation, median, minimum, and maximum. Comparison between binary outcomes will be performed by using Relative Risks (RRs), whereas for continuous data, the difference of means (DMs) will be used. Comparisons involving time to event data will be displayed by using Kaplan-Maier survival curves and summarised by Hazard Ratios (HRs).

All measures of association will be presented with their 95% confidence interval. A result will be considered as statistically significant if its p-values will be less than 0.05 (5%).

The analyses will be performed by using STATA software.

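### Bleeding is compared by arm over the whole hospital stay although the assigned dose ends at first worsening; under the trial's own hypothesis this can dilute the contrast behind a claim of similar major bleeding

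*Protocol*

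**What the plan says.** The Synopsis sets as part of the primary objective that the high dose be "Similar in terms of major bleeding risk during hospital stay". Its Statistical Considerations compare the arms on "the proportion of participants who experience at least one bleeding event (major or non-major) during their hospital stay". Section 4.2 adds "All patients enrolled in the study will be entered in the full analysis set independently of his/her treatment time" and "The intention to treat population will be considered for primary analysis". No other analysis population is named and no margin for similarity is given.

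Exposure ends earlier than the count. Under Criteria for discontinuing or modifying allocated interventions, enoxaparin at the assigned dose "will last until the hospital discharge, or up to the occurrence of any event included in the primary outcome". Duration of treatments lists the stopping events: infarction, thromboembolism, escalation of ventilatory support, major bleeding, an adverse event or clinical condition judged by the physician, and death. It then says "The decision about what type and dose of antithrombotic treatment to administer, after the interruption of assigned dose of Enoxaparin, will be left" for the treating physicians to make. The trial is open label, and follow-up runs to discharge (Duration of follow-up).

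The protocol records the time of each bleed (2.4.3 and the secondary safety endpoint), the dates and reasons for stopping, and the antithrombotics given afterwards. It states no use of the last two in the bleeding comparison.

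**The concern.** From first worsening to discharge, patients in both arms may receive any antithrombotic at any dose, yet a first bleed in that period is charged to the randomised arm. Low-dose patients who have a thromboembolism may well move to more intense anticoagulation, since exclusion criterion 9 itself names venous thromboembolism as an indication for anticoagulant treatment.

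For a superiority question, dilution of this kind makes success harder. Here the wanted conclusion is similarity, so dilution makes success easier. If the high dose works as hoped, fewer of its patients enter the uncontrolled phase, and part of a real excess of bleeding on the higher dose could be hidden.

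**Working it through.** **Planning figures.** Synopsis and section 2.6: 300 patients, 1:1, two-sided alpha 5%, 80% power, control worsening 25-30%, 50% relative reduction. The usual two-proportion formula with pooled variance gives 304 in total for 25% vs 12.5% (79.5% power at 150 per arm) and 242 for 30% vs 15% (87.9% power). The stated 300 is therefore reproduced at the lower control rate, and the worsening shares below are the ones the trial was sized on.

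**Patients leaving the assigned dose through worsening.** Low dose: 150 × 0.25 to 0.30 = 38 to 45. High dose: 150 × 0.125 to 0.15 = 19 to 23. Patients whose first event is death are included in these numbers but add no off-dose time.

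**Inputs for bleeding.**
- Low-dose major bleeding b_L = 1.4% to 2.29%; high-dose b_H = 2.7% (section on Risk/benefit Ratio). Relative risk (RR) = 2.7/2.29 to 2.7/1.4 = 1.18 to 1.93. Risk difference (RD) = 0.41 to 1.30 points.
- Worsening w_L = 27.5% (midpoint of 25-30%), w_H = 13.75% (half of it).
- Share of the stay remaining after worsening, s = 0.8: **assumed**.
- Bleeding risk r on physician-chosen treatment, expressed for a full stay and equal in both arms: **assumed**, 2.7%, 5% or 10%.

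**Formula.** Off-dose time replaces on-dose time, so arm risk = b × (1 − w·s) + r × w·s. Here w·s = 0.22 (low) and 0.11 (high):
- Low dose = 0.78·b_L + 0.22·r
- High dose = 0.89 × 2.7 + 0.11·r = 2.403 + 0.11·r

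| r | Low dose (%) | High dose (%) | RR |
|---|---|---|---|
| none (on-dose) | 1.40-2.29 | 2.70 | 1.18-1.93 |
| 2.7% | 1.69-2.38 | 2.70 | 1.13-1.60 |
| 5% | 2.19-2.89 | 2.95 | 1.02-1.35 |
| 10% | 3.29-3.99 | 3.50 | 0.88-1.06 |

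**When does the sign reverse?** Setting the arms equal gives r = b_L + (b_H − b_L) × 0.89/0.11. That is 5.6% for b_L = 2.29% and 11.9% for b_L = 1.4%. Both exceed twice the largest bleeding figure in the protocol.

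**When does the contrast shrink?** The same formula gives RD = (b_H − b_L) × 0.89 − (r − b_L) × 0.11. For any r at or above b_L the difference is below its on-dose value.

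**Other worsening patterns (s = 0.5 to 0.8 unless stated).**
- Equal worsening, 25% or 30% in both arms: from 1.30, RD falls to 0.99-1.14 points whatever r is.
- High dose worsens more (30% vs 15%), s = 0.8, r = 5-10%: RD grows from 1.30 to 1.42-2.02 points, though RR is 1.78-1.83, slightly below 1.93. From 0.41, RD grows to 0.64-1.24 and RR rises from 1.18 to 1.24-1.38.
- r = 0 at the planned worsening rates: no shrinkage (RD 1.31, or 0.53-0.64 instead of 0.41).

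**Sampling error.** Expected on-dose bleeds per 150: 2.1 to 3.4 (low) and 4.05 (high). The 95% half-width of the RD is 3.2-3.5 points; power is 12% (1.4% vs 2.7%) or 4% (2.29% vs 2.7%).

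**The case against.** A whole-stay intention-to-treat count is a legitimate treatment-policy comparison: it asks what bleeding follows from starting on each dose under ordinary care. That stands, and a reader who inferred that this analysis is an error would go too far.

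Supportive safety analyses commonly sit in the SAP, which is not shown, and the data for one are collected. This also has force. But the protocol itself fixes the window, the population and the similarity objective, and does not say whether that objective must also hold on the assigned dose.

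A reader might infer that the bias always runs towards similarity, or that the share leaving the dose differs by design. Neither holds. The share differs only if the efficacy hypothesis is true, and the direction can change if the high dose worsens more or later treatment bleeds less.

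A reader might also simply add r to a full-stay on-dose risk and conclude that the high dose will look safer. That counts the same days twice: at r = 2.7% the high-dose arm would total 2.7 + 0.1375 × 2.7 = 3.07%, although every day carries the 2.7% risk.

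Finally, sampling error exceeds the dilution. True, but random error does not excuse a systematic pull towards the wanted answer, and with no margin and few events similarity is already easy to assert.

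**Conclusion.** The point holds in a conditional form. If the low dose worsens at least as often as the high dose, as the trial assumes, and later treatment is at least as bleeding-prone as the low dose, the whole-stay count dilutes the dose contrast towards similarity. In the illustration RR moves from 1.18-1.93 to 1.13-1.60 or 1.02-1.35 at post-stop risks of 2.7% or 5%. Apparent reversal (RR down to 0.88) occurs only at the upper end of the assumed range and only for the higher low-dose bleeding figure. The documents do not support saying that the high dose will look safer.

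The size rests on two quantities the protocol does not give: time spent in hospital after worsening and bleeding risk in that time. It also rests on bleeding risks cited from two different settings, hospitalised medical patients for the low dose and outpatients having procedures for the high dose. Letting first-event deaths contribute off-dose time makes the dilution somewhat too large.

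One textual conflict belongs here. The section on discontinuing interventions removes from the study patients who develop a new condition needing anticoagulant or antiplatelet treatment, while section 4.2 keeps everyone enrolled. Read widely, that exclusion could take some off-dose patients out of the very count at issue.

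**What to change.** Keep the whole-stay intention-to-treat comparison and describe it as a treatment-policy comparison. In sections 2.4.3 (Primary safety endpoint, with the secondary safety endpoint) and 4.2, add:

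1. A pre-specified analysis of major and of clinically relevant non-major bleeding on the assigned dose, from first dose to stop of that dose plus one fixed window set before database lock. Analyse it as time to event or per person-time; a plain proportion would give the arm that worsens less a longer time at risk.
2. A rule that bleeding is not described as similar unless both analyses are reported and consistent.
3. A separate listing of later bleeds by the antithrombotic actually received.
4. Wording that reconciles the exclusion of patients with new anticoagulant or antiplatelet indications with intention to treat, so that they stay in the whole-stay count.

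The cost is protocol or SAP wording and one or two extra tables from data already collected. The downside is that the on-dose analysis has few events and its stopping is informative, so it supports the whole-stay analysis and cannot replace it. No rule on treatment after the stop is proposed.
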